### A priori mediator measures, at 7 weeks

Acceptance and Action Questionnaire (AAQ-II): the AAQ measures psychological flexibility using a 7-item scale [36]Values Questionnaire (VQ): 10-item self-report measure assessing the extent to which one lives consistently with their values [37]Committed Action Questionnaire (CAQ): the CAQ 8-item measure is derived from an original scale of 24 items [38]. Committed action is goal-directed, flexible persistenceBeliefs about emotions scale (BAE): this 12-item scale represent types of beliefs about the unacceptability of experiencing and expressing emotions that have been specified in cognitive models [39]

### Participant timeline

The participant timeline is shown in Fig. 1.

**Fig. 1 Fig1:**
[figure not shown]
Participant flow

### Sample size

A total sample size of 266 (133 per arm) would provide 90% power to detect a minimally clinically important effect size (Cohen’s *D*) of 0.4 assuming a 2-sided 5% significance level. The effect size is based on existing literature, determined previously as 0.42 and 0.46 for FACT-G [40, 41]. This effect size represents a difference of 6 points on FACT-G in a cancer population [22]. Assuming each therapist sees 10 participants, an intracluster correlation coefficient (ICC) of 0.01, and allowing for drop-out by 52 weeks of 15%, the estimated total sample size required is 344 (172 per arm) patients to be recruited over 33 months. This represents an average of 10.4 participants per month in total across participating sites. Based on the numbers of patients seen in three sites (845 per annum), this sample size can be achieved assuming a recruitment rate of at least 20% of eligible participants. The sample size assuming independent observations was calculated using the power command in Stata. This was then manually multiplied by the design effect and divided by the proportion expected at follow-up to account for loss to follow-up.

Average estimates of therapist effects for RCTs have been shown to be 0.08, however they are highly variable across studies due to their dependence on the specific outcomes, research design and statistical analysis used [42, 43]. ACT+ uses a manualised approach with structured intervention sessions, and therapists receive training and monthly supervision on its delivery. End of treatment is scheduled for 16 weeks, while the primary outcome of FACT-G score is collected at 52 weeks. These features are likely to reduce therapist effects to negligible levels at the point of primary outcome collection. However, to be conservative we have allowed for the presence of low levels of clustering, estimated at 0.01.

### Methods: assignment of interventions

#### Randomisation

After confirmation of eligibility and collection of informed consent and baseline measures, participants will be randomised to either the intervention or usual aftercare, 1:1. The randomisation will be stratified by broad cancer type (breast, lower gastro-intestinal, urological, haematological, head and neck) and centre (*n* = 6) using different sized randomly permuted blocks. To maintain blinding, the allocation sequence will be generated by a statistician independent to the trial using the ralloc command in stata [44] overseen by the Pragmatic Clinical Trials Unit at Queen Mary (https://www.qmul.ac.uk/pctu/).

#### Concealment mechanism

To maintain allocation concealment, the block sizes used in the sequence generation are unknown to those recruiting participants, and the full randomisation lists are not available to any member of the research team. The randomisation list was integrated into a central REDCap randomisation database which is accessed via the internet to perform a randomisation. Upon entering a participant’s details, the system returns the appropriate allocation in the sequence for that individual.

#### Who will be blinded

Research assistants collecting any outcome data by phone will be blinded to participants’ allocated arm and trial statisticians will be blinded to allocation until finalisation of the statistical analysis plan. The trial manager and the research administrator are the only members of the study team who will be unblinded to ensure that participants randomised to the intervention receive the intervention in a timely fashion.

#### Implementation

The trial manager who is unblinded will receive notifications to randomise eligible participants by the research assistants. Participant details are entered onto the REDCap database once their eligibility has been confirmed.

### Methods: data collection, management, and analysis

#### Plans for assessment and collection of outcomes

The complete list of outcomes is listed in the ‘outcomes’ section above and listed in Fig. 3. Before commencing recruitment, each site receives training on the study design, protocol procedures (via site initiation visit), and data collection procedures (REDCap database training). All members of the site research team are expected to be appropriately trained and work in accordance with GCP guidelines, which is documented in the trial master file (TMF) and investigator site file (ISF).

At baseline, 7 weeks (approximately mid therapy), 16 weeks (approximately end of therapy), and 52 weeks following randomisation, participants will be asked to complete questionnaires related to the outcome measures. Further outcome assessment data will be collected at 2 years after randomisation for participants for whom, before the last recruited participant’s 52-week follow-up time point, would have had 2 years elapse from randomisation. All outcome measures will be collected by either direct participant input into a secure online study-developed database (developed by the QMUL Pragmatic Clinical Trials Unit) or completed via paper questionnaires and returned for data entry by the study team. The questionnaires will not be available in any languages other than English.

#### Health economics

For the economic evaluation, we will combine health and social care costs with the primary outcome measure and quality-adjusted life years (QALYs). Costs will be calculated for the intervention based on therapist time required, and other costs will be derived from the CSRI combined with recognised unit costs. For a societal perspective, informal care and lost employment costs will be valued using average wage rates. QALYs will be estimated using the EQ-5D-5L combined with UK tariffs and using area under the curve methods [35]. Cost differences will be compared between the groups across the whole follow-up period using a regression model with adjustment made for baseline costs. QALY differences will adjust for baseline EQ-5D-5L. Cost-effectiveness will be assessed from a health and social care perspective. If the intervention results in higher costs and better outcomes, then we will divide incremental costs (intervention minus usual care) by incremental QALY to generate an incremental cost-effectiveness ratio. Uncertainty around the cost-effectiveness results will be explored using cost-effectiveness planes and acceptability curves from 1000 cost-outcome combinations from bootstrapped regression models. The cost per unit improvement on the FACT-G will also be calculated. To assess the long-term cost-effectiveness of ACT+, we will develop a decision model using Markov processes. This will entail defining health states over time to which costs and QALYs will be attached. The structure of the model will be developed within the early stages of the programme and will consist of states defined both by clinical severity and quality of life. Costs and probabilities for the model will be derived from published literature, the trial, and expert opinion. The model will be subjected to extensive deterministic and probabilistic sensitivity analyses.

#### Meditators and moderators

Mediation analysis will investigate whether the mechanisms hypothesised to bring about improvements in outcomes after ACT+ (see Fig. 2) can be shown to operate on the primary outcome, QoL as measured by the FACT-G scale, and the secondary outcome of fatigue as measured by the Chalder Fatigue Scale at both 16 and 52. The mediators assessed at 7 weeks (mid-treatment) are commensurate with the theory of ACT+. Mediator analyses will be reported separately following the AGReMA reporting guideline [45].

**Fig. 2 Fig2:**
[figure not shown]
Logic model for the ACT+ intervention

Moderators will include age, gender, type of cancer, severity of depression, and the effects of loneliness and worry in relation to COVID-19 at baseline.

#### Adverse events

All adverse events (AE) and severe adverse events (SAE) as defined (see the ‘Adverse event reporting and harm’ section) will be reported in the trial analysis by arm. In addition, we will report the proportion of patients who deteriorate on the FACT-G and HADS at 52 weeks from baseline, where at least four ACT+ sessions (50%) were delivered (Figs. 2 and 3) [46].

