#### Intervention

ACT is an intervention that aims to increase psychological flexibility. Psychological flexibility refers to an individual’s ability to adapt to demands, shift perspectives, and balance competing desires and needs [16, 23–25]. This means that ACT could help a patient to accept what cannot be changed (e.g. that the cancer might recur), while committing themselves to the things they can change (i.e. meeting their goals in life, irrespective of having had cancer).

We developed the intervention to be integrated with options for work/vocational activity support and exercise in ways that are tailored to each participant’s personal values and goals, and therefore called this ‘ACT Plus (+)’. We also developed a participant handbook and manuals for therapists. The process of developing and refining the ACT+ intervention will be reported separately elsewhere (in preparation).

The intervention is delivered by therapists who had undergone specifically designed training in ACT+ led by the senior study therapist (co-chief investigator TC). Full details of the SURECAN ACT+ training and its evaluation have been published [26]. The core professions of the therapists include clinical psychologists, high intensity therapists (from NHS Talking Therapies), cognitive behaviour therapists trained in ACT, and trained counsellors. Treatment integrity will be assessed at the end of the trial guided by Perepletchikova et al.’s treatment integrity procedures checklist [27].

The sessions can be delivered face-to-face (at the therapist’s main practice), by phone or via online video calls, according to participant preference. The intervention involves up to eight sessions delivered at weekly or fortnightly intervals. Sessions last around 1 h and include homework to be completed prior to the next session. All sessions should take place within a range of 14–20 weeks from a participant being allocated to the intervention arm at randomisation (depending on the frequency of sessions, i.e. weekly or fortnightly, and allowing occasions for missed/rescheduled sessions). Participants are also provided with the ACT+ participant handbook. Eligible participants randomised to the intervention arm will receive the ACT+ intervention in addition to usual aftercare.

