##### Secondary outcomes

The secondary outcomes and mediator measures shown below (unless specified) will be reported at all timepoints: baseline, 7 weeks, 16 weeks, 52 weeks, and 2 years (where applicable). The method of aggregation will be mean scores for both arms. Further details will be presented in the forthcoming statistical analysis plan.The total score of the FACT-G at all other timepointsThe FACT-G sub-scale total scores (physical well-being [range 0–28], social/family well-being [range 0–28], emotional well-being [range 0–24] and functional well-being [range 0–28]. With higher scores indicating better QoLFear of cancer recurrence [29]. Four question self-report scaleThe Impact of Cancer scale (IOCv2): positive and negative impacts subscales [30]Anxiety and depression, measured using the Hospital Anxiety and Depression Scale (HADS) [31]The Chalder Fatigue Scale (CFQ) [32] which is composed of 11 items, each of which is answered using a 4-point Likert scale ranging from 0 (less than usual) to 3 (much more than usual). The maximum score is therefore 33, and a higher score is associated with a worse health stateMeasuring independent physical activity (frequency of occurrences, and duration in minutes) using an modified version of the Godin leisure score index questionnaire [33]The EuroQol (EQ-5D-5L) [34] will be used to measure health-related QoL and to derive quality-adjusted life years (QALYs). The EQ-5D-5L consists of five domains (mobility, usual activities, self-care, pain/discomfort, and anxiety/depression). Each domain is scored between 1 (no problems) and 5 (extreme problems)Health and social care utilisation and use of informal care measured using an adapted version of the Client Service Receipt Inventory [35]. This will cover the three months before randomisation and the periods up to 16-week and 52-week follow-up. The CSRI will be self-completed by participants. We will also collect employment statusEngagement and frequency of engagement in any new meaningful activities (e.g. new work, job, hobbies, or interests) at 16- and 52-week follow-up. This will be analysed as a categorical variable and therefore represented as a descriptive table, for each arm

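### Individual deterioration on FACT-G and HADS is reported only at 52 weeks, although both scales are also collected during therapy and at about its end

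*Protocol article*

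**What the plan says.** The Adverse events section supplements the listed events with a person-level harm measure: "we will report the proportion of patients who deteriorate on the FACT-G and HADS at 52 weeks from baseline", limited to cases "where at least four ACT+ sessions (50%) were delivered". No other time point is given for this proportion.

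Therapy finishes much earlier. The Intervention section states: "All sessions should take place within a range of 14–20 weeks from a participant being allocated to the intervention arm at randomisation". The Sample size section puts it this way: "End of treatment is scheduled for 16 weeks, while the primary outcome of FACT-G score is collected at 52 weeks".

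Questionnaires are completed "At baseline, 7 weeks (approximately mid therapy), 16 weeks (approximately end of therapy), and 52 weeks following randomisation". FACT-G total and HADS are both among the outcomes due at every visit. For those outcomes the Secondary outcomes section says: "The method of aggregation will be mean scores for both arms".

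The section on adverse event reporting and harms restricts collected adverse events to two kinds: exercise injuries where exercise support was part of the intervention, and suicidal ideation. It foresees that participants may become distressed and sends such cases to the lead therapist for action. Distress itself is not on the list of collected events.

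**The concern.** A proportion deteriorating exists to show what a mean cannot: that some people got worse, whatever happened on average. For a talking therapy, one natural period to look at is the therapy itself. The plan collects both scales in that period but takes the person-level count only at the last routine visit.

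A participant who worsens clearly on FACT-G or HADS at 7 or 16 weeks and has recovered by a year is not counted as having deteriorated. Nor is one who worsens early and never returns the 52-week questionnaire. The report could then correctly state that deterioration at one year did not differ between arms, and readers could take that as a statement about the course of treatment, which it is not. What is at stake is the completeness of harm reporting. The primary comparison of FACT-G at 52 weeks is not touched.

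**Working it through.** **1. Distance between therapy and the harm measure.** Inputs: sessions end at week 14 to 20 (Intervention), scheduled end at week 16 (Sample size), deterioration read at week 52 (Adverse events). Gap = 52 − end week; months = weeks × 7 / 30.44.

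- End at week 14: 52 − 14 = 38 weeks, 8.7 months
- End at week 16: 52 − 16 = 36 weeks, 8.3 months
- End at week 20: 52 − 20 = 32 weeks, 7.4 months

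**2. What is reported at each visit.** Setting the Secondary outcomes, Adverse events and assessment sections side by side:

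| Visit | Relation to therapy | FACT-G and HADS collected | Arm means planned | Individual deterioration planned |
|---|---|---|---|---|
| 7 weeks | during | yes | yes | no |
| 16 weeks | about the end | yes | yes | no |
| 52 weeks | 32 to 38 weeks after | yes | yes | yes |

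Suicidal ideation is collected as an adverse event and is not tied to a visit, so it can be recorded during therapy.

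**3. Why the arm means do not fill the two empty cells.** Let a share p of an arm worsen by an average of h points, and let the rest improve by an average of g points. The mean change is (1 − p)g − ph. It is zero or positive whenever p ≤ g / (g + h). If gains and losses are of equal size (g = h), this holds for any p up to one half. An arm mean that is flat or improved is therefore compatible with a substantial minority who got worse. The treatment-by-time models in the Statistical methods section also compare means, so the same limit applies.

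**4. Loss before 52 weeks.** The Sample size section allows 15% drop-out by 52 weeks: 0.15 × 344 = 51.6, about 52 participants, or 0.15 × 172 = 25.8, about 26 per arm. On the plan's own allowance these participants have no 52-week score to compare with baseline. Some may have 7- or 16-week scores; the article does not say how many.

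**5. What cannot be computed.** The article gives no threshold for deterioration in one person and no correlations between visits. The 6 points in the Sample size section are a difference between groups, not a cut-off for one participant. The number of unreported cases cannot be derived from the document.

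**The case against.** There is a good deal on the other side, and much of it stands.

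*Fifty-two weeks is a coherent choice.* It matches the primary endpoint and captures lasting worsening, arguably the more important harm. That stands, and it is a reason to keep the measure. It does not make the measure informative about the therapy period.

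*Psychological harm is covered elsewhere.* A reader might infer that the deterioration count is the trial's only measure of psychological harm. It is not: suicidal ideation is a collected adverse event, and adverse events are reported by arm. A reader might also infer that worsening during therapy would go wholly unseen. It would not: arm means on both scales at 7 and 16 weeks, and the treatment-by-time models, would show an average worsening. What remains unreported is individual worsening short of suicidal ideation. Sending distress to the lead therapist is a safety procedure; the article does not make it an outcome compared between arms.

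*The SAP may deal with it.* The article defers outcome details to the SAP, and nothing in the Adverse events sentence forbids further time points. If the SAP already reports deterioration at 7 and 16 weeks, the point is met. The article, however, names the scales, the baseline and a single time, so it has made a choice that would be followed as written.

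*The 16-week visit is imperfect.* Sessions may run to week 20, so some participants can be in therapy for up to 20 − 16 = 4 more weeks. This counts against making week 16 the main harm comparison. It does not count against reporting it.

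*HADS will not always be there.* Participants unable or unwilling to complete everything may be offered FACT-G, EQ-5D-5L and the service-use inventory alone, so HADS will be missing for them. That limits the HADS rows at any visit where the option is used.

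**Conclusion.** The point holds as a gap in harm reporting that is cheap to close. Followed as written, the plan reports individual deterioration only about 32 to 38 weeks after sessions end. Worsening during therapy that resolves by 52 weeks, or that occurs in someone lost before then, would not appear at the individual level unless it reached suicidal ideation.

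This rests on two readings: that the Adverse events sentence fixes the time point, and that the reporting of arm means in the Secondary outcomes section is all that is planned for these scales at 7 and 16 weeks.

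Two stronger readings are not supported. A reader might take the Sample size remark about negligible therapist effects at 52 weeks to mean that the protocol expects treatment influences to have faded by then. That remark concerns clustering between therapists; the same section powers the trial for an effect of 0.4 on an outcome collected at 52 weeks. A reader might also try to size the problem by simulating scores with no treatment effect and counting those worse at 16 weeks but not at 52. That would measure turnover from ordinary fluctuation, and would show similar turnover in the other direction. It would not measure missed harm. No size is therefore put on the number of cases.

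**What to change.** Keep the 52-week measure. Add to the analysis plan, by randomised arm, the proportion deteriorating on FACT-G and on HADS at 7 and 16 weeks. Use the same threshold at every time, give the between-arm difference with its 95% confidence interval, and read the results descriptively without claims of significance.

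State two limits beside the table: some participants may still be in therapy at week 16, and HADS is missing for those who completed only the reduced questionnaire.

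The added rows should cover all participants with a score in each randomised arm. The four-session condition on the 52-week measure has no counterpart under usual care and is a separate matter that this change does not settle.

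The cost is a sentence or two in the analysis plan and a few table rows, with no new data collection, visits or participant burden. The downside is a few more descriptive harm comparisons, some of which will differ between arms by chance.

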**Methods:**

We will conduct a multi-centre, pragmatic, theory driven, randomised controlled trial. We will assess whether ACT+ including usual aftercare (intervention) is more effective and cost-effective than usual aftercare alone (control). The primary outcome is QoL of participants living with or beyond cancer measured using the Functional Assessment of Cancer Therapy: General scale (FACT-G) at 52 weeks. We will recruit 344 participants identified from secondary care sites who have completed hospital-based treatment for cancer with curative intent, with low QoL (determined by the FACT-G) and randomise with an allocation ratio of 1:1 to the intervention or control. The intervention (ACT+) will be delivered by NHS Talking Therapies, specialist services, and cancer charities. The intervention consists of up to eight sessions at weekly or fortnightly intervals using different modalities of delivery to suit individual needs, i.e. face-to-face sessions, over the phone or skype.

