#### Criteria for discontinuing or modifying allocated interventions

Intervention arm participants may discontinue receiving the intervention at any point they request.

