### Statistical methods

#### Statistical methods for primary and secondary outcomes

Prior to any analysis taking place, a statistical analysis plan will be developed and made publicly available, containing a more detailed and technical description of the analysis to be performed. To ensure transparency and reproducibility, its content will follow the guidelines proposed by Gamble et al. [47].

The analysis will be reported in line with the CONSORT guidelines and the extension for non-pharmacologic treatment interventions [48]. Baseline demographic and clinical outcomes will be summarised by treatment group. Normally distributed data will be summarised by mean (standard deviation); non-normally distributed data will be presented as median (interquartile range) and categorical variables presented as *n* (%).

The analysis will follow intention-to-treat principles, where participants with available data are included in the treatment group to which they were randomised. Hypothesis tests will be two-sided and estimated treatment effects will be accompanied by a 95% confidence interval. For all analyses, a significance level of 5% will be used.

The primary analysis will be a mixed effects linear regression of the total FACT-G score at 52 weeks with a random effect for therapist, fixed effects for baseline score, and randomisation stratification factors. Secondary outcomes will be modelled similarly.

To explore the treatment effects over time, the analysis will be repeated with multilevel mixed effects models with a nested structure to include an additional random effect for individual, a fixed effect for time, and an interaction between treatment and time. Safety data will be summarised by treatment group.

Predictors of costs and cost-effectiveness will also be identified, the latter being calculated as the monetary value of QALYs minus therapy costs. Generalised or standard linear models will be used as appropriate.

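### The FACT-G/HADS deterioration measure counts only cases with four or more ACT+ sessions, so the arms are not comparable on it and harm may be understated

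*Protocol article*

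**What the plan says.** The Adverse events section has two parts. Adverse events and SAEs "will be reported in the trial analysis by arm", with no condition on attendance. A further measure is then added: the proportion of patients who "deteriorate on the FACT-G and HADS at 52 weeks from baseline, where at least four ACT+ sessions (50%) were delivered".

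Four other statements in the article bear on this measure:

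- Intervention: "The intervention involves up to eight sessions delivered at weekly or fortnightly intervals". Four sessions are therefore half the maximum.
- Criteria for discontinuing or modifying allocated interventions: "Intervention arm participants may discontinue receiving the intervention at any point they request".
- Abstract, Methods: the trial asks whether "ACT+ including usual aftercare (intervention) is more effective and cost-effective than usual aftercare alone (control"). Controls have no ACT+ sessions.
- Statistical methods for primary and secondary outcomes: "The analysis will follow intention-to-treat principles, where participants with available data are included in the treatment group to which they were randomised". The same section adds: "Safety data will be summarised by treatment group".

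The article states no deterioration proportion for all randomised participants, in either arm.

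**The concern.** The session condition is met or missed after randomisation, and only in one arm. It has two consequences.

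First, selection. Participants may leave ACT+ whenever they wish, and those who leave before session four drop out of the measure. Some of them may have left because they felt worse, and a harm measure should keep those people in.

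Second, there is no valid comparator. Read literally, controls have no deterioration figure, and the ACT+ proportion has nothing to be judged against. If the figure is instead set beside all controls, a selected part of one arm is compared with the whole of the other, and the protection of randomisation is lost.

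The measure carries more weight here because the other harm data are narrow. Under Adverse event reporting and harms, the only adverse events collected are suicidal ideation and exercise injuries where exercise support formed part of the intervention. SAEs go to the sponsor only if the lead therapist judges them related and unexpected. Psychological worsening short of suicidal ideation would show as a proportion only through the deterioration measure.

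**Working it through.** **The plan's own figure.** The article gives no expected deterioration rate or attendance rate. The only figure in the sentence is the 50%, which agrees with the Intervention section: 4/8 = 50%. The sample size does not depend on this measure.

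**Inputs from the article (Sample size).** 172 participants per arm and 15% drop-out by 52 weeks, so about 172 × 0.85 = 146 ACT+ participants with 52-week data.

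**Assumed inputs (not in the article).**
- f, the share of those 146 with fewer than four sessions: 10% to 40%.
- p₁, the proportion deteriorating among those with four or more sessions: 15%.
- p₀, the proportion deteriorating among those with fewer than four: 5% to 45%.

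**Formulas.**
- Rate reported under the restriction = p₁.
- Rate in all randomised ACT+ participants with data = (1 − f) × p₁ + f × p₀.
- Error (second minus first) = f × (p₀ − p₁). A positive value means harm is understated.

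**Worked case.** With f = 20%, 146 × 0.20 ≈ 29 people are left out. With p₀ = 30%, the as-randomised rate is 0.80 × 0.15 + 0.20 × 0.30 = 18.0%, against 15.0% reported, which is 3 points understated.

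**Range.** As-randomised ACT+ rate, against a reported 15.0% in every cell:

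| Share with <4 sessions (number left out) | p₀ = 5% | p₀ = 15% | p₀ = 30% | p₀ = 45% |
|---|---|---|---|---|
| 10% (15) | 14.0% | 15.0% | 16.5% | 18.0% |
| 20% (29) | 13.0% | 15.0% | 18.0% | 21.0% |
| 30% (44) | 12.0% | 15.0% | 19.5% | 24.0% |
| 40% (58) | 11.0% | 15.0% | 21.0% | 27.0% |

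The extremes are 0.40 × (0.05 − 0.15) = −4 points (overstated) and 0.40 × (0.45 − 0.15) = +12 points (understated). The error is zero when the two groups deteriorate equally often.

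**Comparability.** This part needs no assumed rates. The criterion counts ACT+ sessions and controls have none, so no control subset corresponds to the ACT+ subset, whatever the values of f, p₀ and p₁.

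**The case against.** The strongest reply is that the restriction touches one supplementary, descriptive item. Adverse events and SAEs are reported by arm without it, and mean FACT-G and HADS scores are planned for both arms and modelled under intention to treat. A reader might infer that the trial's main harm summary is restricted in this way. The article does not support that, and on this the reply stands. It does not remove the defect, because few adverse events are collected and a mean can improve while a minority gets worse.

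A reader might also infer that harm is understated as a matter of fact. The article does not establish this. It gives neither the attendance nor the rates, and people who never started, or who left because they were well, could push the error the other way. Deterioration is also judged at 52 weeks, long after sessions should have ended (14–20 weeks from allocation), so early worsening need not persist to the assessment. Understatement is plausible but not shown.

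A third tempting inference is that equal true harm would appear as an advantage for ACT+, for instance by the 3 points of the worked case. That needs both the assumed rates and a between-arm contrast, and the article states no such contrast for this measure. On the literal reading there is no control figure, so no spurious benefit can arise.

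Finally, the intention-to-treat statement sits under methods for primary and secondary outcomes, and the article plans adherence and attendance analyses elsewhere. Those, however, are sensitivity analyses beside an as-randomised analysis. Here the attendance-based version is the only one stated, and the same section says that safety data are summarised by treatment group. The sentence also cites a source for its approach, which is not available to this review. A rationale there might explain the threshold of four but could not supply a control counterpart.

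**Conclusion.** The point holds as a should-fix. The deterioration measure is conditioned on attendance after randomisation, leaves out ACT+ participants with fewer than four sessions, and has no counterpart among controls. The arms are therefore not comparable on it. This follows from the text alone and does not depend on the direction of any bias.

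The size and direction do rest on assumptions. Over the assumed ranges the ACT+ rate could be anywhere from 4 points overstated to 12 points understated, so the supportable statement is that harm may be understated. These figures also treat f as the share among participants with 52-week data. If early leavers are followed up less often, fewer of them enter the calculation.

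The primary outcome, the sample size and the by-arm reporting of adverse events and SAEs are unaffected.

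**What to change.** State that the proportion deteriorating on FACT-G and on HADS from baseline to 52 weeks will be reported for all randomised participants with data, in the arm to which they were allocated, as a risk difference with 95% CI. Keep the four-session subset only as a supplementary description of the ACT+ arm, shown beside those with fewer than four sessions and with the number in each group. The score change that counts as deterioration can be left to the SAP.

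The comparison will be imprecise and should be presented as descriptive. With 15% in both arms and 146 per arm, the half-width of the interval is about 1.96 × √(2 × 0.15 × 0.85 / 146) ≈ 8 points, ignoring therapist clustering.

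The cost is a change of wording and a small additional table, settled before analysis. FACT-G and HADS are already collected at baseline and 52 weeks in both arms, so no new data are needed, and neither treatment nor sample size changes.
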